#### Guidelines given in the CRF

'Treatment interruption' is defined as when a treatment is stopped and resumed within 18 hours. In the case of treatment interruption the CRF will be continued and the treatment that follows will be considered in the context of the preceding one. The only exception is when, after RRT interruption, the modality is changed (see below under 'Case report form: Change modality (step 3)'; Fig. 2).

'Treatment end' is defined as when a given RRT is stopped because of clinical or other factors for more than 12 hours or when clinical or other factors have changed since the start of RRT. Should the patient be started on another RRT, then the latter shall be considered a new one.

In the case that the modality is changed, a new CRF will need to be filled in (see 'Criteria to change RRT'). This will be followed by a new CRF 'Modality-specific assessment time' (also see Table 1).

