#### Case report form: Criteria to initiate RRT (step 2)

This CRF will automatically provide the patient's consecutive number. The user must enter the date and time when the following clinical events (indexed numerically) occurred:

• 1. Oliguria (urine output <200 ml/12 hours),

• 2. Anuria (urine output <50 ml/12 hours),

• 3. High urea/creatinine,

• 4. Hyperkalaemia (>6.5 mmol/l or rapidly rising potassium),

• 5. Metabolic acidosis,

• 6. Fluid overload,

• 7. Hyperthermia (>41°C),

• 8. Immunomodulation,

• 9. What RIFLE (Risk Injury Failure Loss of function End stage renal disease) criteria [12] are applicable?

• 10. Others (to specify)

The user will also be asked to prioritize the criteria (from 1 to 3) when two or more specified. In addition, the modality chosen must be specified (defined as following and indexed numerically)

• 1. CVVH (as defined as ≤ 35 ml/kg per hour ultrafiltration rate in postdilution or <40 ml/kg per hour in predilution),

• 2. CVVHDF (defined as use of dialysate + replacement [define]),

• 3. High volume haemofiltration (defined as >35 ml/kg per hour in postdilution or >45 ml/kg per hour in predilution),

• 4. Pulse high volume haemofiltration (from 85 ml/kg per hour to 100 ml/kg per hour for 6–8 hours, followed by CVVH at 35 ml/kg per hour),

• 5. Coupled plasma filtration adsorption (CPFA) plus CVVH ,

• 6. IHD ('intermittent' includes conventional haemodialysis and slow extended daily dialysis, thereby encompassing all treatments in which sessions are separated from one another for 10 hours or more).

The CRF will then permit the user to specify any other relevent criteria, including the following:

• Staff problems,

• Technical problems,

• Product (e.g. fluids, lines, filters, machine) availability problems,

• Logistics,

• Others (to be specified).

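### Same-modality stops of more than 12 and up to 18 hours count as both an interruption and an end of treatment; separately, predilution haemofiltration at 40–45 ml/kg per hour has no modality class

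*Protocol article*

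**What the plan says.** **Stop rules (Guidelines given in the CRF).** A treatment interruption "is defined as when a treatment is stopped and resumed within 18 hours"; in that case "the CRF will be continued and the treatment that follows will be considered in the context of the preceding one". The one stated exception is a change of modality after the interruption. A treatment end "is defined as when a given RRT is stopped because of clinical or other factors for more than 12 hours". A second limb of the same definition, with no time limit, also makes it an end if circumstances differ from those at the outset. Any RRT begun after an end counts as a new treatment.

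**Modality classes (Case report form: Criteria to initiate RRT, step 2).** In predilution, CVVH is defined by the limit "or <40 ml/kg per hour in predilution" and high volume haemofiltration by ">45 ml/kg per hour in predilution". In postdilution the two classes share the boundary of 35 ml/kg per hour.

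**What is recorded (Modality-specific assessment time, step 3).** Dates and times of interruption, resumption and end are captured. Prescribed effluent, where the form asks for it, is tied to assessment time 0 for CVVH. Total effluent is taken at time 24 or at the last assessment before an interruption or end.

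**How dose is derived (Calculation of dialysis dose).** Clearance follows the transport mechanism: ultrafiltration rate times sieving coefficient for convection, and experimentally constructed relationships for diffusive and mixed techniques. Nothing is said about hours off treatment.

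**The concern.** The abstract names delivered dose as the primary end-point, and clearance is the single predictor in the power calculation. The Conclusion and Key messages list the causes of down-time as an aim, and the Discussion treats the divergence of delivered from prescribed dose as an important unknown. All of these depend on knowing where one treatment stops and the next begins.

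For same-modality stops in the 12–18 hour range the guideline gives two incompatible answers. Two centres could both follow it and return different records for the same care. The unclassified predilution band is a smaller fault of the opposite kind: there two definitions overlap, here neither applies.

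**Working it through.** **1. Stop definitions side by side (same modality resumed)**

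| Length of stop | Interruption (within 18 h) | End by duration (more than 12 h) |
|---|---|---|
| up to 12 h | yes | no |
| more than 12 h, up to 18 h | yes | yes |
| more than 18 h | no | yes |

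The middle row is the contradiction. The second limb of the end definition, a change in clinical or other factors, carries no time limit, so it does not resolve that row.

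**2. What changes whatever the dose formula.** Take 24 h of treatment, a 15 h stop, then 24 h of the same modality.
- Filed as an interruption: one treatment, one time 0, one set of prescribed values. If down-time means time off within a treatment, it is 15 of 24 + 15 + 24 = 63 h, or 24%.
- Filed as an end: two treatments, two time 0 records, two sets of prescribed values and, on the same reading, no down-time.

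**3. The plan's own yardstick (Statistical analysis, Primary end-point).** Inputs: event rates 0.51 and 0.25 at clearances 29.8 and 35.0, SD 10.0, n = 110, two-sided alpha 0.01.
- Odds ratio = (0.25/0.75)/(0.51/0.49) = 0.320; relative risk = 0.25/0.51 = 0.490.
- Slope = ln(0.320)/5.2 = −0.219 per unit.
- Power = Φ(2.2 × √(110 × 0.51 × 0.49) − 2.576) = Φ(11.53 − 2.58) = 1.00. Simulation (2,000 runs) also gives 1.00.

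The stated figures reproduce. The contrast of 35.0 − 29.8 = 5.2 serves as the yardstick. The clearance there carries no unit; ml/kg per hour is assumed.

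**4. Possible effect on dose.** *Assumption, not in the protocol:* stopped hours are in the denominator for an interruption and outside it for an end. With rate r, treated hours T and stop g, the average is r × T/(T + g) for an interruption and r for an end, so the difference is r × g/(T + g). The 12 h column is the limiting value, since an end needs more than 12 h.

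| r (ml/kg per hour) | Treated hours | g = 12 h | g = 15 h | g = 18 h |
|---|---|---|---|---|
| 35.0 | 12 + 12 | 11.7 | 13.5 | 15.0 |
| 35.0 | 24 + 24 | 7.0 | 8.3 | 9.5 |
| 35.0 | 48 + 48 | 3.9 | 4.7 | 5.5 |
| 35.0 | 72 + 72 | 2.7 | 3.3 | 3.9 |
| 29.8 | 12 + 12 | 9.9 | 11.5 | 12.8 |
| 29.8 | 72 + 72 | 2.3 | 2.8 | 3.3 |

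Worked cell: 35 × 48/63 = 26.7, a difference of 8.3. The difference equals 5.2 when T = g × (r/5.2 − 1); at r = 35 and g = 15 that is 15 × 5.73 = 86 treated hours. Shorter courses exceed the planning contrast and longer ones do not.

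**5. Effect on the primary regression.** Dose was multiplied by 48/63 in a random 10%, 25% or 50% of simulated patients. Power stayed 1.00, and the mean fitted slope moved from −0.23 to −0.21, −0.20 and −0.20.

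**6. Predilution bands.** Rates of 39.9, 40, 42, 45 and 45.1 fall in CVVH, none, none, none and high volume respectively. Both labels are convective and the dose section does not treat them differently, so the label does not alter the computed dose.

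**The case against.** The strongest reply is that the records allow repair. Stop, resumption and end times are collected, so one denominator could be applied centrally however a centre filed the stop. This largely stands for dose and down-time, but the repair is partial. Prescribed values tied to time 0 are collected afresh only if the stop is filed as an end. The timing of effluent totals follows the filing, and the 1 to 12 hour assessments on the continuous forms are optional. A closed CRF can be corrected only on written request (Materials and methods).

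It can also be said that nothing shows centres would in fact diverge, and that Figure 2 and Table 1, not available here, may illustrate how stops are handled. That limits confidence in the practical consequence. It does not remove the conflict between the two written definitions.

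Several stronger readings are tempting but not supported:
- *A dose shift larger than the planning SD.* A reader might take a 48 h course containing a 15 h stop and compute 35 × 33/48 = 24.1 against 35, a difference of 10.9. That needs the unstated denominator rule and a short course. If dose means clearance while treatment is running, the answer is 35 either way.
- *The band gap changes delivered dose or loses patients.* It does neither on the text: the computation is the same for both labels, and the CVVH form records effluent regardless.
- *A third conflicting rule for intermittent dialysis.* The 10-hour wording, "all treatments in which sessions are separated from one another for 10 hours or more", describes which modalities count as intermittent. It is not clearly a rule for cutting treatment into units.
- *Loss of power.* The simulation shows none, although it covers random misfiling only, not misfiling that tracks centre.

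**Conclusion.** The point holds as an internal inconsistency. For same-modality stops of more than 12 and up to 18 hours, the guideline requires both continuing the treatment and starting a new one. The certain consequence is that treatment units, the assessment clock with its time 0 prescriptions, and counted down-time are not uniquely defined for those stops.

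An effect on delivered dose is conditional. It needs the denominator assumption in step 4 of the working and a reading of planning clearance as ml/kg per hour. It then runs from about 2 to 15 ml/kg per hour over the courses tried, and lies on either side of the 5.2-unit contrast according to course length. The harm is to the validity of the exposure and the down-time description, not to power. How often such stops occur is not given, so the aggregate effect cannot be sized.

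The 40–45 ml/kg per hour predilution gap is a separate, smaller defect confined to descriptive modality classification.

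**What to change.** Before official recruitment opens, ideally during the two-month CRF familiarisation period:

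1. Reconcile the interruption and end definitions so that every stop falls under exactly one of them, including how the untimed change-of-factors clause interacts with the time limits.
2. Reconcile the predilution limits for CVVH and high volume haemofiltration so that every rate has exactly one class.
3. State one denominator for delivered dose, and derive dose and down-time centrally from the recorded stop and restart times rather than from how the centre filed the stop.

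The values are for the sponsor to choose; what matters here is that the rules be mutually exclusive and exhaustive. The cost is CRF guideline wording and a sentence in the dose section. No additional data are needed.

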**Conclusion:**

The study will hopefully help to collect useful information on the current practice of renal replacement therapy in ICUs. It will also provide a centre-based collection of data that will be useful for monitoring all aspects of extracorporeal support, such as incidence, frequency, and duration.

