## Key messages

• 	Choice of RRT in renal and nonrenal indications

• 	Delivered dose of dialysis and its impact on outcome measures (primary end-point)

• 	Hemodynamic response to RRT (secondary end-point)

• 	Causes for down-time in CRRT

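### A short same-modality stop that follows a change in clinical or other factors meets both the interruption and the treatment-end definitions, and aligning the two hour limits would not cure this

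*Protocol article*

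**What the plan says.** All the rules stand in the protocol article under Guidelines given in the CRF.

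- **Interruption.** It "is defined as when a treatment is stopped and resumed within 18 hours". There is no lower limit and no condition on the patient's clinical state. The consequence is continuity: "In the case of treatment interruption the CRF will be continued and the treatment that follows will be considered in the context of the preceding" (that is, the earlier treatment).
- **Exception.** "The only exception is when, after RRT interruption, the modality is changed". A change in the clinical situation is not listed as an exception.
- **End, first limb.** The RRT is "stopped because of clinical or other factors for more than 12 hours".
- **End, second limb.** "or when clinical or other factors have changed since the start of RRT". No stop length is given, and neither the factors nor the size of the change is specified. If RRT is then started again, it counts as a new treatment.

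The outputs that depend on these boundaries are also stated. Key messages lists "Causes for down-time in CRRT", and the main Conclusion asks for the reasons for down-time. The Conclusion of the Abstract names a use of the database: "monitoring all aspects of extracorporeal support, such as incidence, frequency, and duration".

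**The concern.** The interruption rule leaves a clinical change out of its exceptions. The end rule then uses a clinical change as a boundary. A centre that stops a circuit for a short time and resumes the same modality, when something relevant has changed since the start, can follow the guidance and either continue the record or close it and open a new one.

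The choice has consequences in the CRF. Under Modality-specific assessment time (step 3), the prescribed duration and blood flow rate are entered at assessment time 0, as is the prescribed effluent for CVVH and CVVHDF. The mandatory CRRT assessments between start and end fall at 24 hours and its multiples; those at 1, 3, 6 and 12 hours are optional. SOFA during treatment is collected only at 24 hours and multiples. A new record restarts this clock. Counts of treatments, duration per treatment and down-time within a treatment could then differ between centres because of coding rather than practice. Closed CRFs can be corrected only on written request (Materials and methods), so such differences would tend to persist.

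**Working it through.** The plan gives no figure to reproduce here, and no power or alpha calculation enters. The check applies the two definitions to stops of different lengths.

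**Inputs** (Guidelines given in the CRF): interruption if 0 < stop ≤ 18 h; end by the first limb if stop > 12 h; end by the second limb if factors have changed. The same modality is resumed throughout, so the modality exception does not apply.

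**Step 1. Classification, with the second limb read as needing a stop of any length**

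| Stop | No change in factors | Factors changed |
|---|---|---|
| above 0 to 12 h | interruption only | interruption and end |
| above 12 to 18 h | interruption and end (first limb) | interruption and end |
| above 18 h | end only | end only |

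The middle row is the 12 h versus 18 h overlap and exists without the second limb. The top right cell comes from the second limb alone, so bringing the two hour limits into line leaves it in place.

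**Step 2. Do other readings of the second limb remove the overlap?**

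- *No stop needed at all.* The overlap is the same, and a change in factors during uninterrupted treatment is also an end.
- *The 12-hour limit carries over to the second limb.* The short-stop overlap goes, but the second limb then adds nothing to the first.
- *Only a different modality counts as another RRT.* The overlap goes, but modality change already has its own rule here and under the 'Change to modality' CRF, so the limb adds little.
- *Factors means only the reasons for starting RRT.* Fewer stops are caught, but a short stop after the indication has changed, with the same modality resumed, still meets both definitions.

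The readings that remove the overlap leave the second limb with little or no function, and the text does not state any of them.

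**Step 3. What the label changes.** This is a hypothetical course, not taken from the document: 72 h of CVVH with three stops of 2 h, all after a change in factors.

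- All coded as interruptions: 1 treatment of 72 h; down-time 3 × 2 = 6 h; 6/72 = 8.3%.
- All coded as ends: 4 treatments; running time 72 − 6 = 66 h; mean duration 66/4 = 16.5 h; down-time within a treatment 0 h.
- One coded as an end: 2 treatments; 72 − 2 = 70 h inside treatments; down-time 4 h; 4/70 = 5.7%.

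If the four runs are of equal length (16.5 h each), none reaches 24 h, so no in-treatment SOFA falls due. Coded as one treatment, assessments at 24 h and 48 h are mandatory.

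**The case against.** The strongest reply is that the text can be read sensibly. Criteria to initiate RRT (step 2) records clinical events and then other criteria such as staff, technical and logistic problems. The factors in the end rule may refer back to those, so that the second limb means RRT stopped because its indication has changed. A one- or two-hour circuit stop is not that. The sentence on the sole exception can also serve as a tie-breaker: same modality, resumed within 18 hours, hence an interruption. Fig. 2 and Table 1, to which the guidance refers, are not available here and may settle the matter.

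Part of this stands. The narrower reading is plausible and would make the problem less frequent. But the guidance does not state it, and the exception sentence sharpens the conflict as much as it resolves it, because the next paragraph adds a second way out without saying which rule prevails.

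Three stronger inferences are tempting and are not supported.

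- *Almost every running treatment meets the second limb, because RRT itself changes potassium, pH, urea and fluid status.* This needs the broadest meaning of factors. The document gives no frequency.
- *Down-time will be misreported or lost.* Start, interruption, resumption and end times are CRF fields, so a gap between two records can largely be rebuilt. Down-time is declared as causes or reasons, not as a percentage, and factors complicating RRT have their own field whatever the label. The percentages above only illustrate how far a label can move such a statistic.
- *The coding is related to outcome and biases the dose–mortality analysis.* This is conceivable, but nothing in the document shows it.

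**Conclusion.** The point holds as a contradiction in a stated rule, not as missing detail. A same-modality stop resumed within 18 hours after a change in clinical or other factors is both an interruption and an end, with no clear precedence. For stops of up to 12 hours the second limb alone causes this.

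The effect is on descriptive outputs: number of treatments, duration per treatment, down-time within a treatment and which assessment times fall due. Its size is unknown, because it depends on how centres read the word factors and on how often such stops occur. The sample size is untouched, and no effect on the primary analysis of clearance against event rate is shown. The recorded times limit the damage, but they cannot supply a SOFA value that was not collected because the record closed before 24 hours.

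The conclusion rests on the guidance text as printed; Fig. 2 and Table 1 could clarify it. It deserves correction before centres are compared, at moderate priority.

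**What to change.** 1. Reconcile the two definitions so that each stop has exactly one classification. This includes settling the 12- and 18-hour limits against each other; which limit applies is for the investigators to decide.
2. Record a changed clinical situation as a reason field, not as a boundary of the treatment record.
3. Before reporting down-time, duration and frequency, derive CRRT episodes and gaps centrally from the recorded start, interruption, resumption and end times with that single rule. Apply it also to records already closed, so that the result does not depend on the centre's label.
4. Keep IHD sessions as separate units under the definition in Criteria to initiate RRT (step 2), where sessions may be only 10 hours apart. A common gap rule would merge sessions spaced 10 to 12 hours apart under the lower limit, or 10 to 18 hours apart under the higher, and distort frequency and duration.
5. Check that Fig. 2 and Table 1 agree with the revised wording.

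The cost is one line of CRF guidance and one derivation step. Rebuilding episodes needs no new data, and patient care does not change.

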#### Case report form: 'Change to modality'

Each centre will be asked to define the clinical/practical reasons for changing a modality. The change to modality may be necessary after treatment is interrupted. In this case, the following treatment will be considered a new treatment. This CRF aims to provide information on why the modality was chosen. It is similar to the CRF: Criteria to initiate RRT.

#### Case report form: Outcome (step 4)

At discharge of the patient, the following information should be provided:

• SAPS II (all sets of data; previous 24 hours before discharge from ICU),

• SOFA (all set of data; previous 24 hours before discharge from ICU),

• IHD needed in ward (yes/no),

• Creatinine at discharge (μmol/l; mg/%),

• Urea at discharge (μmol/l; mg/%),

• In-ICU mortality (yes/no),

• Ventilation days (number of days),

• 28-day mortality (yes/no),

• Discharged from ICU (date),

• Discharged from hospital (date),

• Hospital survival (yes/no),

• Date of last RRT session.

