If we are to understand how dialysis doses are actually delivered in routine clinical practice in ICUs, an observational clinical study is needed to confirm how, to what extent and with what clinical indication the different modalities of RRT are administered. With this in mind we have initiated the DOse REsponse Multicentre International collaborative initiative (DO-RE-MI) trial. The primary end-point of DO-RE-MI is mortality (ICU mortality, 28-day mortality and hospital mortality), and the secondary end-point is the haemodynamic response to RRT, expressed as percentage reduction in noradrenaline (norepinephrine) requirement to maintain blood pressure.

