## Materials and methods

Figure 1 presents a study flowchart. Only incident patients with an indication for RRT will be recruited. The study is intended to describe current practices of RRT in all patients admitted to ICUs who are in need of RRT, with or without ARF. All data listed herein will be entered in electronic case report forms (CRFs) that are available via the internet [11]. The following rules will be applied without exception:

First, all patient data will be entered anonymously. To this aim, each centre will have a code, and patients will be consecutively assigned a unique number. Under no circumstances will there be any written or oral transmission of data that may make it possible to identify any patient. Failure to adhere to this will be followed by cancellation of the data from the website by the webmaster.

Second, data for each patient will be entered in a separate CRF. These data may be copied from paper CRFs in order to make the reporting of data from bed to computer station easier. All fields may be amended at any time until the patient's CRF is completed and closed. At this point, one may access the patients' CRF but it will be no longer be possible to amend the CRF. In the case of overt inconsistency, corrections must be detailed in writing (e-mail) by the person responsible for data quality for the centre or by the center itself. In all cases, no corrections will be permitted in the absence of an express written request. The person responsible for data quality will have access to the centre's CRF in printed form only. A registry will collect correspondence between the person responsible for data quality and the centre.

Third, completion of some fields in the CRF is mandatory. Failure to complete them will prevent progression to the following CRF and closure of the opened CRF. Failure to complete a CRF electronically will result in the patient being excluded from the study.

Finally, Each centre will be able to open CRFs for its own patients but never CRFs for patients from other centres.

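### The outcome form is to be completed at discharge but asks for 28-day mortality, which cannot be known then for patients who leave hospital alive before day 28

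*Protocol article*

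**What the plan says.** In the protocol article, the section on the step 4 outcome form opens with its timing: "At discharge of the patient, the following information should be provided". The list that follows includes "28-day mortality (yes/no", "Discharged from ICU (date", "Discharged from hospital (date" and "Hospital survival (yes/no", together with in-ICU mortality, ventilation days and the date of the last RRT session. It has no date of death, no date last known alive and no unknown category.

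The Introduction gives the field its weight: "The primary end-point of DO-RE-MI is mortality (ICU mortality, 28-day mortality and hospital mortality". The Abstract instead makes delivered dose the primary end-point, but it too lists 28-day mortality among the outcomes to be compared with dose.

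Materials and methods sets the editing rules: "All fields may be amended at any time until the patient's CRF is completed and closed". It continues: "At this point, one may access the patients' CRF but it will be no longer be possible to amend the CRF". Corrections after closure are described for overt inconsistency and need a written request. Some fields, not named, are mandatory, and a patient whose form is not completed electronically is excluded.

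**The concern.** Discharge is a natural time to record ICU and hospital outcome. It is the wrong time to record status at a fixed day that may lie in the future. A centre that follows step 4 as written, for a patient going home on day 12, is asked a yes/no question about day 28 that it cannot yet answer. If it enters no, the entry looks plausible beside a record of hospital survival, so it would not stand out as an overt inconsistency. With no death date on the form, the end-point cannot be rebuilt from the database later.

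At stake is one of the three mortality measures to be related to dialysis dose. In patients discharged early, the field could report status at hospital discharge under a 28-day label. Centres that follow up patients and centres that do not would be recording different things.

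A second gap is that the article gives no day 0 for the 28 days, although it records both ICU admission and RRT start.

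**Working it through.** **1. Who is affected.** The form asks for hospital discharge date and hospital survival, so it cannot be finished before the hospital stay ends. Taking patients by their course:

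- Died in hospital by day 28: status known at completion.
- Still in hospital at day 28: status known at completion.
- Left hospital alive before day 28: status not known at completion.

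Only the third group is exposed. ICU mortality and hospital mortality are known for everyone by then.

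**2. Whether the editing rules close the gap.** Fields stay open until closure, so a centre may wait until day 28. Nothing requires it to wait, and the article describes no status check after discharge. Once the form is closed, the correction route is described only for overt inconsistency.

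**3. Illustrative size of misclassification.** The article gives neither the share *s* of patients leaving hospital alive before day 28 nor the fraction *d* of those who die by day 28. Both are assumed here. With N = 162 (the recruitment target), missed deaths = N × s × d, and the understatement of 28-day mortality is s × d.

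- s = 20%: 0.20 × 162 = 32 patients. With d = 5% to 15%, 2 to 5 deaths are missed, or 1 to 3 percentage points.
- s = 40%: 0.40 × 162 = 65 patients. With d = 5% to 15%, 3 to 10 deaths are missed, or 2 to 6 percentage points.

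As a check on s, suppose the planning event rate of 0.51 is hospital mortality (the article does not say which mortality it is). Then 0.49 × 162 = 79 patients leave hospital alive. The two values of s mean that 32/79 = 41% or 65/79 = 82% of them leave before day 28, so the upper value is high.

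**4. Whether power is the issue.** The plan's own figures reproduce from its inputs (event rates 0.51 at clearance 29.8 and 0.25 at 35.0, SD 10.0, n = 110, two-sided alpha 0.01):

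- Odds ratio = (0.25/0.75)/(0.51/0.49) = 0.320.
- Beta = ln(0.320)/5.2 = -0.219.
- Relative risk = 0.25/0.51 = 0.490.
- Power = Φ(|beta × SD| × √(n p(1-p)) - z) = Φ(2.19 × √(110 × 0.51 × 0.49) - 2.576) = Φ(8.9) = 1.00. Simulation of the likelihood-ratio test also gives 1.00.

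Now take 0.51 as the 28-day rate, assume that 20%, 50% or 80% of 28-day survivors have unverified status, and drop them. That removes 110 × 0.49 × share = 11, 27 or 43 patients. The apparent event rate, 0.51/(0.51 + 0.49 × (1 - share)), becomes 0.57, 0.68 or 0.84. Simulated power is 1.00, 1.00 or 0.96. Power barely moves, but the recorded mortality does. Leaving such patients out biases the rate upwards, whereas coding their later deaths as survival biases it downwards.

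**5. Day 0.** For a patient who starts RRT on ICU day 10, a window counted from ICU admission leaves 28 - 10 = 18 days after RRT start. A window counted from RRT start leaves 28.

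**The case against.** The strongest reply is that the article does not lock the form at discharge. The lock follows closure, a centre may hold the form open, and 28-day status may be among the unnamed mandatory fields that block closure. The guide to CRF compilation (Table 1), the online forms and the full protocol are not shown, so a day-28 check and a time origin may be set out there. This stands against several stronger readings that a reader might draw:

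- **That forms are locked at discharge, or that a centre has no choice but to enter no.** The text says neither. A default no is a risk.
- **That everyone leaving the ICU before day 28 is affected.** The hospital fields on the same form rule this out.
- **That 28-day mortality becomes a duplicate of another measure.** Even with in-hospital ascertainment only, it differs from hospital mortality for in-hospital deaths after day 28, and from ICU mortality for ward deaths before day 28.
- **That the error is related to dose.** This is possible if discharge habits and dosing both vary by centre, but the document gives no evidence for it.
- **That no day-28 contact exists.** The article describes none, which does not prove absence.

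What the reply does not remove is the timing that step 4 states. The article prints the outcome form field by field and ties its completion to discharge. That instruction does not fit a 28-day field, whatever another document adds.

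**Conclusion.** The point holds in a limited form. The stated completion time cannot yield a true 28-day answer for patients discharged alive from hospital before day 28, and neither the listed fields nor the editing rules ensure that the answer is obtained later. Post-discharge deaths before day 28 may be recorded as survival, and practice may differ between centres.

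The size cannot be derived from the document. The range of 1 to 6 percentage points rests wholly on the assumed shares (20% to 40% leaving hospital alive before day 28, 5% to 15% of them dying by day 28) and on every such death being missed. The consequence is bias in one component of the primary end-point, not a material loss of power. The missing day 0 is a related ambiguity, and the document gives no basis for preferring one origin over the other.

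**What to change.** - Change the step 4 timing so that the 28-day and hospital fields are completed, and the form closed, no earlier than the later of hospital discharge and day 28, unless the patient has died.
- Add date of death or date last known alive, and derive 28-day mortality from the dates.
- Allow unknown as an answer, so that an untraced patient is neither entered as no by default nor excluded for an incomplete form.
- State one day 0 for the 28 days, either ICU admission or first RRT start. Both are already recorded.

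If the full protocol or the CRF guide already contains these rules, the step 4 text needs only to be brought into line with them. Otherwise the change should be made before official recruitment begins, because deaths that nobody looked for may not be recoverable later. Data are anonymous, so only the centre can trace them.

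The cost is one date field, a changed closing rule in the electronic form, and a vital-status check by the centre for patients discharged alive before day 28. Some of these patients will remain unknown.
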